**Table 3 Outcomes of 96-week follow-ups.**

|  | Control group | MMF group | RR | P value |
|--|---------------|-----------|----|----------------|
|  |               |           |    |                |

|                                            | (n=)                  | (n=)                  |          |
|--------------------------------------------|-----------------------|-----------------------|----------|
|                                            | Mean (SD) or
N (%) | Mean (SD) or
N (%) | (95% CI) |
| Primary outcome, %                  |                       |                       |          |
| Proportion of severe flares                |                       |                       |          |
| Proportion of mild to moderate flares      |                       |                       |          |
| Severe flares, %                    |                       |                       |          |
| Lupus nephritis                            |                       |                       |          |
| Neuropsychiatric symptoms                  |                       |                       |          |
| Rash (prednisone dose > 0.5mg/kg/day)      |                       |                       |          |
| Pleurisy                                   |                       |                       |          |
| Thrombocytopenia (<60* 10  /L) |                       |                       |          |
| Pulmonary arterial hypertension            |                       |                       |          |
| Hemolytic anemia                           |                       |                       |          |
| Fever (prednisone dose > 0.5mg/kg/day)     |                       |                       |          |
| Henoch-Schonlein purpura                   |                       |                       |          |
| Moderate mitral insufficiency              |                       |                       |          |
| Arthritis (prednisone dose > 0.5mg/kg/day) |                       |                       |          |

**Mild to moderate flares,  
%**

Arthritis

Rash

Oral ulcer

Fever

Leukopenia  
( $1.5-4 \times 10^9/L$ )

Thrombocytopenia  
( $60-100 \times 10^9/L$ )

**Secondary outcome, %**

Proportion of LLDAS,  
%

SLEDAI-2000 score at  
last visit

Prednisone at last visit  
(mg)

---

LLDAS: Lupus low disease activity state; SLEDAI: Systemic lupus erythematosus  
disease activity index;

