### **3. Study outcomes**

#### **3.1 Primary Endpoint:**

The primary outcome was the proportion of patients who have flares (mild to moderate flares and severe flares) defined by modified SELENA-SLEDAI Flare Index (SFI)  at 96 weeks of follow-up.

The definition of mild to moderate flare is the fulfillment of one or more following items:

- 1) variation of SELENA-SLEDAI score  $\geq 3$  (but  $< 12$ );
- 2) new or worsening rashes, cutaneous vasculitis, nasopharyngeal ulcers, serositis, arthritis or fever caused by lupus;
- 3) increase in the dose of prednisone, but less than 0.5mg/kg/day;
- 4) increase of nonsteroidal anti-inflammatory drugs or HCQ;
- 5) Physician's Global Assessment (PGA) (0-3 scale)  $\geq 1$ .

Severe flare is defined as the fulfillment of one or more of the following items:

- 1) change in SELENA-SLEDAI score of more than 12;

- 2) new or worsening central nervous system involvement, vasculitis, nephritis, myositis, thrombocytopenia (platelet  $<60 \times 10^9/L$ ) or haemolytic anaemia (haemoglobin  $<70g/L$  or decrease in haemoglobin level  $>30g/L$ );
- 3) increased usage of prednisone (doubled in dosage or more than 0.5mg/kg/day);
- 4) added cyclophosphamide, azathioprine, methotrexate, mycophenolate mofetil or hospitalization because of lupus activity;
- 5) PGA  $>2.5$ .

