### 3.2 Secondary Endpoint:

- 1) The proportion of lupus low disease activity state (LLDAS) at week 96.
- 2) Short form-36 (SF-36) score of before and after treatment in two groups.
- 3) The proportion of adverse events of two groups in the follow-ups.
- 4) Changes in SLEDAI-2000 score.
- 5) Changes in prednisone dose.

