## 4. Study design

In this study, we randomly assigned patients (1:1) to Control group and MMF group. Control group received treatment with HCQ (5mg/kg/day) and prednisone (0.5mg/kg/day); while MMF group received treatment with HCQ (5mg/kg/day) and prednisone (0.5mg/kg/day) plus MMF 500mg twice daily. The dose of MMF stayed the same unless a contrary or severe adverse event occurred.

Prednisone dose was tapered as follows:

Initial dose (0.5mg/kg/day) maintained for four weeks

[figure not shown]

tapered 5mg every two weeks till to 20 mg/day

↓

tapered 5mg every month

↓

gradually to 0.1-0.2mg/kg/day

The taper of prednisone doses was determined by the physicians according to the assessment of patients.

Notes:

- 1) Patients with severe flare were not involved in subsequent treatment plan, but they were still being followed up consistently until the end of the entire process.
- 2) Patients who met the criteria of severe flare were treated with increased doses of prednisone (more than 0.5mg/kg/day), immunosuppressive therapy or hospitalized for treatment according to the patients' condition and the physician's assessment.
- 3) Patients with mild to moderate flares continued to be followed up till the end of Week 96, and all flare episodes were recorded.
- 4) Patients with mild to moderate flares could increase the dose of prednisone (less than 0.5mg/kg/day) or nonsteroidal anti-inflammatory drugs.
- 5) For fever, rash, and arthritis, the dose of prednisone could be used at an initial dose of less than 0.5mg/kg/day, and following the assessment of symptoms, the dose could be increased to more than 0.5mg/kg/day if needed.
- 6) Any sign of kidney involvement (glomerular haematuria and/or cellular casts, proteinuria >0.5g/24hours (or spot urine protein-to-creatinine ratio (UPCR) >500mg/g), unexplained decrease in glomerular filtration rate (GFR)), renal biopsy was suggested to confirm the diagnose of LN. Results of renal biopsy were confirmed by a senior nephrologist ([name]). The treatment of LN was provided according to the European Renal Association-European Dialysis and Transplant Association (ERA-EDTA) guideline.
- 7) The treatment of other organ involvement was provided following the 2019 European League Against Rheumatism (EULAR) recommendation.

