### **8.6 Secondary outcomes**

Secondary Endpoint including:

- 1) The proportion of lupus low disease activity state (LLDAS) at week 96.
- 2) Short form-36 (SF-36) score of before and after treatment in two groups.
- 3) The proportion of adverse events of two groups in the follow-ups.
- 4) Changes in SLEDAI-2000 score.
- 5) Changes in prednisone dose.

In descriptive statistics, data were expressed in the form of frequency (percentages) for categorical variables (proportion of LLDAS, proportion of adverse events (AEs)), medians (interquartile) or means  $\pm$  standard deviations (SD) for continuous variables (SF-36 score variation, SLEDAI-2000 score variation and prednisone dose).

In addition, t-tests were used to compare between-group differences in continuous variables after exploring the normality of data distribution using the Shapiro-Wilk test. Mann-Whitney U tests were used to compare continuous variables with a skewed distribution. Pearson Chi-square or Fisher's exact tests were used to compare between-group differences in categorical variables. All tests were performed two-sided at the significance level of 0.05.

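### Endpoint 5 is a change in prednisone dose, but Table 3 shows only a last-visit value in mg, compared without adjustment although dosing is per kg: an avoidable loss of precision

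*Combined protocol and SAP*

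**What the plan says.** SAP 3.2 lists endpoint 5 as "Changes in prednisone dose", without unit, baseline or time point. SAP 8.6 groups it with two change scores, as "SF-36 score variation, SLEDAI-2000 score variation and prednisone dose"; only the first two are worded as variation. In SAP section 15, Table 3 has one row for it, "Prednisone at last visit", and gives the unit as mg. That is the only unit the plan states for this endpoint.

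The comparison is unadjusted: a t-test when the data look normal, otherwise "Mann-Whitney U tests were used to compare continuous variables with a skewed distribution". SAP 8.6 adds: "All tests were performed two-sided at the significance level of 0.05".

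Dosing is largely per kg. SAP 4 gives "Initial dose (0.5mg/kg/day) maintained for four weeks" and ends the taper "gradually to 0.1-0.2mg/kg/day". A mild-to-moderate flare can be met by an "increase in the dose of prednisone, but less than 0.5mg/kg/day" (SAP 3.1). Between start and target, however, the taper moves in 5 mg steps with a breakpoint at 20 mg/day, and physicians decide its course.

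Body weight is not a row in the Table 1 shell, nor a named item in the schedules (protocol 7.6, SAP 12). Physical examination may capture it, but the documents do not say so.

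**The concern.** Two patients who follow the taper identically can differ in mg only because one is heavier. With a start of 0.5 mg/kg/day and a final dose near 0.15, the fall in mg is about 0.35 times body weight before any treatment effect. An unadjusted mg comparison leaves that spread in the error term, and Table 1 would not show a chance imbalance in weight.

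The definition is also open. Patients enter without prior SLE treatment (inclusion criterion 3). If baseline means the dose at entry, it is zero for everyone and the change equals the last-visit dose. If it means the starting dose, the change is dominated by a weight-driven quantity. The two readings differ greatly in precision.

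Endpoint 5 is the only endpoint that measures steroid dose directly, and protocol 2.2 cites reduced glucocorticoid use as part of the case for MMF.

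**Working it through.** **The plan's own figure.** SAP 6 assumes flare rates of 10% and 30% with 58 per arm, and reports power 0.8036 and actual alpha 0.0568. Exact enumeration of the unpooled Z test gives 0.80357 and 0.05678, and 58/0.9 = 64.4, rounded up to 65. It reproduces, but it concerns flares only. The documents give no SD, effect or power for prednisone, and no weight distribution.

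**Do the absolute steps remove weight from the end dose?** On the written taper, a 60 kg patient starts at 30 mg, reaches 20 mg at about week 6 and 10 mg at about week 14. A 90 kg patient starts at 45 mg, reaches 20 mg at about week 12 and 15 mg at about week 16. Both are then at 0.167 mg/kg/day, inside the target band before the first visit at week 24. The steps shape the path; nominally, the per-kg band governs the end.

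**Share of variance.** Assumptions, not in the documents: weight W has mean 60 kg and SD 8 to 12; the final per-kg dose d has mean 0.15 and SD 0.04 to 0.06, independent of W.

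- Var(change in mg) = 0.35² × Var(W) + E(W²) × Var(d)
- Var(last-visit mg) = 0.15² × Var(W) + E(W²) × Var(d)

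| SD of W, SD of d | Weight term, change | Weight term, last visit | Dose term | Weight share, change | Weight share, last visit |
|---|---|---|---|---|---|
| 8, 0.06 | 0.1225 × 64 = 7.84 | 0.0225 × 64 = 1.44 | 3664 × 0.0036 = 13.19 | 7.84/21.03 = 37% | 1.44/14.63 = 10% |
| 12, 0.04 | 0.1225 × 144 = 17.64 | 0.0225 × 144 = 3.24 | 3744 × 0.0016 = 5.99 | 17.64/23.63 = 75% | 3.24/9.23 = 35% |

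**Power.** Assume MMF lowers d by half its SD, with 65 complete patients per arm. Power ≈ Φ(Δ/(σ√(2/65)) − 1.98), with √(2/65) = 0.1754 and σ² averaged over the arms.

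- *SDs 8 and 0.06*: Δ = 60 × 0.03 = 1.8 mg; MMF mean d = 0.12.
  - Change: σ² = (21.03 + 0.38² × 64 + 13.19)/2 = 21.73, so Φ(2.20 − 1.98) = 59%.
  - Last visit: σ² = (14.63 + 0.12² × 64 + 13.19)/2 = 14.37, so Φ(2.71 − 1.98) = 77%.
  - Adjusted for starting dose: σ² = 13.19, so Φ(2.83 − 1.98) = 80%.
- *SDs 12 and 0.04*: Δ = 60 × 0.02 = 1.2 mg; MMF mean d = 0.13.
  - Change: σ² = (23.63 + 0.37² × 144 + 5.99)/2 = 24.67, so Φ(1.38 − 1.98) = 27%.
  - Last visit: σ² = (9.23 + 0.13² × 144 + 5.99)/2 = 8.83, so Φ(2.30 − 1.98) = 63%.
  - Adjusted: σ² = 5.99, so Φ(2.79 − 1.98) = 79%.
- *mg/kg/day*: Φ(0.5/0.1754 − 1.98) = 81% in both settings.

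Simulation over the whole grid (2,000 trials per setting) gave 28–58% for change, 65–76% for last visit, 78–81% adjusted and 80–82% in mg/kg: the same picture.

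**How far the assumptions move it.** With mean weight 58 kg and weight CV 12–20%:

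- Final doses uniform over 0.1–0.2 mg/kg: last-visit share 28–51%, or 17–38% after rounding to 5 mg tablets.
- Widely varying final doses (per-kg CV 50–80%): last-visit share 2–13%.
- Change in mg, per-kg CV 19–80%: share 11–85%.
- Maintenance fixed at 5, 7.5 or 10 mg whatever the weight: last-visit share 0%. Dividing by weight then adds noise. With weight CV 17%, the dose CV rises from 27.2% to 32.8%, so 80% power in mg becomes Φ(2.80 × 27.2/32.8 − 1.96) = Φ(0.36) = 64% in mg/kg.

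With 58 per arm, simulated adjustment gained about 9–49 points over unadjusted mg change and 2–15 over unadjusted last-visit mg in weight-scaled scenarios. It cost nothing measurable with fixed maintenance doses, where mg/kg lost 10–21 points against last-visit mg.

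**The case against.** A reader might infer that analysing in mg hides a steroid-sparing effect. The documents do not support that. Weight precedes randomisation and is balanced in expectation, so the mg comparison is unbiased for the mg difference; only precision is lost.

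A reader might also infer that weight supplies much of the variance of the row in Table 3. That cannot be shown. The large shares belong to the mg change, and the only unit the plan gives is attached to the last-visit value. Physician discretion, dose increases for flares and continued follow-up after severe flare would all widen the last-visit distribution. With the group difference generated by the plan's 30% and 10% flare rates, and flaring patients placed at 0.2–0.5 mg/kg (an assumption), power was 53–65% in last-visit mg and 59–69% in mg/kg, a gap of only 4–8 points.

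Nor do the documents make mg the wrong scale. The taper steps, the 20 mg/day breakpoint and the tablets are in absolute mg, the severe-flare rule includes a weight-free doubling criterion, and protocol 2.2 states infection risk by mg per day. Someone interested in steroid exposure can reasonably want mg.

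These objections stand, and they rule out replacing mg by mg/kg. They do not answer the mismatch between a change endpoint and a last-visit row, or justify leaving out an inexpensive covariate. The power figures above also assume t-tests and complete data; the plan allows Mann-Whitney tests and expects 10% dropout.

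**Conclusion.** The point holds as a matter of definition and precision. Endpoint 5 is named a change, tabulated as a last-visit value in mg, and compared without adjustment although the starting dose in mg is proportional to weight by design. The mismatch rests on the documents alone.

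The size of the loss rests on assumptions. Under the 60 kg model, unadjusted power is about 27–59% for mg change and 63–77% for last-visit mg, against 79–80% with adjustment. For the last-visit dose the loss shrinks towards nil if maintenance is set in fixed mg.

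This is a free improvement of low severity on one secondary endpoint. The primary endpoint and its sample size are unaffected.

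**What to change.** In SAP 3.2, 8.6 and Table 3:

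- Define endpoint 5 as prednisone dose in mg/day at week 96 compared with baseline, and state that baseline means the starting dose, since patients enter untreated.
- Keep mg/day as the scale and analyse it by ANCOVA, with starting dose in mg or baseline weight as covariate. One suffices, because the two are nearly proportional. Weight is the safer choice if starting doses are prescribed after allocation is known.
- Show mg/kg/day as a supporting analysis, divided by baseline weight; later weight may itself respond to treatment.
- Add baseline weight to Table 1.

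The cost is minor SAP wording, one covariate and, if not already captured, one CRF item. Medication is already scheduled for recording at screening (SAP 12), and weight must be known to prescribe per kg. No extra patients or visits are needed.

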**Table 4 Adverse events.**

|                         | Control group | MMF group  | P value |
|-------------------------|---------------|------------|----------------|
|                         | (n=) N (%)    | (n=) N (%) |                |
| Total AEs, %            |               |            |                |
| Infection               |               |            |                |
| Upper respiratory tract |               |            |                |
| Pneumonia               |               |            |                |
| Lower urinary tract     |               |            |                |

Herpes zoster virus

Candida

Tuberculosis

Gastrointestinal event

Bone fracture

Osteonecrosis of the femoral  
head

Other events

**Table 5. The comparison of SF-36 scores before and after treatment.**

SF-36: Short Form-36; PF: Physical functioning; BP: Bodily pain; MH: Mental

|                  |                     | PF | BP | MH | RP | VT | SF | GH | RE | HT | MCS | PCS |
|------------------|---------------------|----|----|----|----|----|----|----|----|----|-----|-----|
| Control
group | Before
treatment |    |    |    |    |    |    |    |    |    |     |     |
|                  | After
treatment  |    |    |    |    |    |    |    |    |    |     |     |
|                  | Change
in score  |    |    |    |    |    |    |    |    |    |     |     |
|                  | Before
treatment |    |    |    |    |    |    |    |    |    |     |     |
| MMF
group     | After
treatment  |    |    |    |    |    |    |    |    |    |     |     |
|                  | Change
in score  |    |    |    |    |    |    |    |    |    |     |     |

health; RP: Role physical; VT: Vitality; SF: Social functioning; GH: General health;  
RE: Role emotional; HT: Reported health transition; PCS: Physical component  
summary; MCS: Mental component summary.

**Table 6. The comparison of organ damage according to The Systemic Lupus International Collaborating Clinics (SLICC)/American College of Rheumatology (ACR) Damage Index (SDI) for SLE.**

|           | Control group (n=) N
(%)/ mean (SD) | MMF group (n=) N
(%)/mean (SD) | p value |
|-----------|----------------------------------------|-----------------------------------|----------------|
| SDI, %    |                                        |                                   |                |
| SDI, mean |                                        |                                   |                |

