**Research Interventions:** In this study, new-onset SLE patients were screened. Participants who met the inclusion criteria were randomly assigned (1:1) by the Department of Rheumatology and Immunology of Ruijin hospital to receive either MMF (MMF group) or control (Control group). Control group received treatment with HCQ (5mg/kg/day) and prednisone (0.5mg/kg/day); while MMF group received treatment with HCQ (5mg/kg/day) and prednisone (0.5mg/kg/day) plus MMF 500mg twice daily. The first follow-up of treatment was at week 24, and then every 24 weeks for a total of 96 weeks. The primary endpoint was the proportion of SLE patients having flares (mild-to-moderate flare and severe flare) according to SELENA-SLEDAI Flare Index. The secondary endpoints included: 1) The proportion of lupus low disease activity state (LLDAS) at week 96; 2) Short form-36 (SF-36) score before and after treatment; 3) The proportion of adverse events in the two groups during follow-up; 4) Changes in SLEDAI-2000 score; 5) Changes in prednisone dose.

**Study Duration:** September 2018 to September 2021

**Subject participation time:** 96 weeks per subject from screening enrollment to completion of all follow-up visits

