### **7.1.4 Items and times of clinical and laboratory examinations to be carried out**

Patients were observed for clinical manifestations, assessment of disease condition, detection of liver and kidney function, erythrocyte sedimentation rate (ESR), CRP, blood and urine routine, anti-dsDNA antibody levels, complement C3, C4, immunoglobulin, SLEDAI-2K score, SF-36 score, medication use, and adverse reaction (AEs) records.

Number of visits: at screening + 4 follow-up visits (week 24, 48, 72, 96).

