## 12.2 SF-36 questionnaire

### 12.2.1 SF-36 questionnaire Chinese version

## SF-36 量表

请用画圈“√”的形式，选择符合您目前状态的内容。谢谢您的配合！

1、总体来讲，您的健康状况是：

- ①非常好    ②很好    ③好    ④一般    ⑤差

2、跟1年以前比您觉得自己的健康状况是：

- ①比1年前好多了    ②比1年前好一些    ③跟1年前差不多

- ④比1年前差一些    ⑤比1年前差多了

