### 12.2.2 SF-36 questionnaire

## SF-36 QUESTIONNAIRE

( 1992 -- Medical Outcomes Trust)

Patient Name: \_\_\_\_\_

Date: \_\_\_\_\_

1. In general, would you say your health is: (circle one)

Excellent      Very good      Good      Fair      Poor

2. Compared to one year ago, how would you rate your health in general now? (circle one)

Much better now than one year ago.

Somewhat better now than one year ago.

About the same as one year ago.

Somewhat worse than one year ago.

Much worse than one year ago.

3. The following items are about activities you might do during a typical day. Does your health now limit you in these activities? If so, how much? (Mark each answer with an **X**)

| ACTIVITIES                                                                                   | Yes,
limited
a lot | Yes,
limited a
little | No, not
limited
at all |
|------------------------------------------------------------------------------------------------------------|-----------------------------------|--------------------------------------|---------------------------------------|
| a. Vigorous activities , such as running, lifting heavy objects, participating in strenuous sports  |                                   |                                      |                                       |
| b. Moderate activities , such as moving a table, pushing a vacuum cleaner, bowling, or playing golf |                                   |                                      |                                       |
| c. Lifting or carrying groceries                                                                           |                                   |                                      |                                       |
| d. Climbing several flights of stairs                                                               |                                   |                                      |                                       |
| e. Climbing one flight of stairs                                                                    |                                   |                                      |                                       |

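### Table 5 of the SAP treats the SF-36 health-transition item as a before-after change score, although the item is already a comparison with one year ago and does not measure change since baseline.

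*Combined protocol and SAP*

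**What the plan says.** SAP section 15, Table 5, is headed "The comparison of SF-36 scores before and after treatment". It has 11 columns: eight SF-36 scales, the mental and physical component summaries, and HT, which the footnote spells out in "RE: Role emotional; HT: Reported health transition". Each arm has rows for the score before treatment, the score after treatment and the change.

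SAP section 8.6 lists the continuous secondary variables as "SF-36 score variation, SLEDAI-2000 score variation and prednisone dose". It says that "t-tests were used to compare between-group differences in continuous variables" once normality has been explored, with Mann-Whitney U for skewed data, two-sided at 0.05. Neither document gives HT a different analysis.

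HT is item 2 of the questionnaire. The English form in protocol appendix 12.2.2 reads "Compared to one year ago, how would you rate your health in general now". The Chinese form in appendix 12.2.1 has the same one-year anchor: "跟1年以前比您觉得自己的健康状况是".

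The SF-36 is scheduled at every visit. Protocol section 7.1.4 gives "Number of visits: at screening + 4 follow-up visits (week 24, 48, 72, 96", and participation lasts "96 weeks per subject from screening enrollment to completion of all follow-up visits".

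**The concern.** The eight scales and two summaries describe health at or near the visit: their items ask about the present or about the past four weeks (one month in Chinese item 9). Subtracting the screening value from a later value gives change since baseline. Item 2 is different, because the patient has already made a comparison over one year. Subtracting one such answer from another does not give change since baseline, although Table 5 presents it as the same kind of quantity.

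The trial asks whether early MMF improves long-term prognosis. An early gain that lasts would be a favourable answer, and it is the pattern that a late transition rating is least able to show. A null HT column beside the other scores could be read as evidence against a quality-of-life benefit.

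**Working it through.** The plan states no figure for HT, so there is nothing of its own to reproduce first. The group size used below is the planned one: 58/0.9 = 64.4, rounded up to 65 per arm (SAP section 6).

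**Step 1: the week each answer looks back to.** Reference week = visit week − 52.

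| Visit (week) | Reference week |
|---|---|
| 0 (screening) | −52 |
| 24 | −28 |
| 48 | −4 |
| 72 | 20 |
| 96 | 44 |

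**Step 2: what the change row contains.** Let H(w) be health at week w. With week 96 as the after visit,

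HT change = [H(96) − H(44)] − [H(0) − H(−52)].

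An ordinary scale gives H(96) − H(0).

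**Step 3: the between-arm difference.** Let B(w) be the expected MMF minus Control difference in health at week w. Randomisation makes B(0) and B(−52) zero in expectation, so

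- ordinary change: B(96)
- HT change: B(96) − B(44).

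For a benefit D complete by week 44 and held to week 96, the HT difference is D − D = 0. For linear growth it is D × (96 − 44)/96 = 0.54 D. For a benefit arising only after week 44 it is D. These results need only a literal reading of the one-year recall.

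**Step 4: illustrative size.** The documents give no SF-36 effect or SD. Assumed: D = 0.5 SD, latent SD 1, correlation 0.5 between any two time points, 65 per arm, two-sided 0.05. Within-person variance is then 0.5 per time point. The ordinary change uses two time points (variance 1) and HT change uses four (variance 2). Treating HT as continuous, power ≈ Φ(δ√(65/2) − 1.96), with √32.5 = 5.70:

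- ordinary change: δ = 0.5, and Φ(2.85 − 1.96) = 81%
- HT, early sustained benefit: δ = 0, so rejection is at the 5% level
- HT, linear growth: δ = 0.271/√2 = 0.192, and Φ(1.09 − 1.96) = 19%
- HT, benefit after week 44: δ = 0.5/√2 = 0.354, and Φ(2.02 − 1.96) = 52%.

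Simulation with HT cut into five levels (4,000 runs; for the late pattern, assumed cut-points at ±0.5 and ±1.5 SD) agrees:

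| Pattern of benefit | Ordinary change | HT change |
|---|---|---|
| complete by week 24, sustained | 80% | 5% |
| complete by week 48, sustained | 80% | 6% |
| linear to week 96 | 81% | 20% |
| only after week 44 | 80% | 51% |

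**Step 5: other assumptions.** With 58 per arm, a benefit of 0.6 latent units, SD 0.7 within and between persons and recall noise of SD 0.5, the figures are 90% against 5% (complete by week 24), 89% against 5% (complete by week 44), 90% against 21% (linear) and 90% against 53% (after week 44). The ordering is the same.

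**The case against.** Several points can fairly be made for the plan.

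- **The after visit is not dated.** Neither Table 5 nor SAP section 8.6 names it. Week 96 is attached only to LLDAS, and Table 3 reports other secondary outcomes at the last visit. If week 48 were meant, the item would look back to about week −4 and most of the problem would go. This stands: week 96 is an inference from the end of follow-up. Even at week 48, however, subtracting the screening answer still yields a difference of two transitions.
- **A formal test of HT is not explicit.** Table 5 has no P value column, while Tables 3, 4 and 6 do. The test comes from the general rule in section 8.6. That also stands, but nothing exempts HT, and the change row is mislabelled with or without a test.
- **Some benefits would show.** The sample size assumes flare rates of 10% and 30%. Control-arm flares after week 44 would lower week-96 HT in that arm. A reader might infer that HT loses most of its power whatever the pattern. The late-onset case does not support that: 51% against 80% is a loss of about 30 points, against about 75 for an early sustained benefit.
- **Reversal is not shown.** A reader might also infer that HT would favour Control. The formula permits it if the gap narrows after week 44, but this needs a Control arm that does badly early and recovers late. Nothing in the documents suggests that, and it was not computed.

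**Conclusion.** The point holds in a limited form. As written, the HT change row does not measure change since baseline. That follows from the item wording in both languages and the layout of Table 5, whichever visit is used.

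The further result, that the expected between-arm difference is zero for a benefit complete by about week 44 and constant afterwards, rests on week 96 being the after visit and on literal one-year recall. The power figures rest in addition on an assumed effect, correlation and response categories, and serve only to show scale.

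The consequence is small. One of 11 columns of one of five secondary outcomes is affected. A reader might conclude that the SF-36 endpoint as a whole is compromised. It is not: the eight scales and both summaries can show a sustained benefit, and the primary outcome and sample size do not depend on HT.

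**What to change.** 1. Take HT out of the change rows of Table 5, and add to SAP section 8.6 that the SF-36 variation tests cover the eight scales and the two component summaries only.
2. If HT is kept, report the five-level answer by arm at week 48, compared between arms as it stands, without subtracting the screening answer. The one-year recall then reaches back to about baseline (week −4). It says nothing about benefit after week 48, which the other scores cover.
3. State which visit is meant by after treatment in Table 5 and section 8.6.

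The cost is one table column and a sentence or two in the SAP. Week-48 SF-36 data are already scheduled, so no collection changes. The downside is one fewer change score to report.
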